# Psychosomatic therapy for patients frequently attending primary care with medically unexplained symptoms, the CORPUS trial: study protocol for a randomised controlled trial

**DOI:** 10.1186/s13063-019-3913-3

**Published:** 2019-12-09

**Keywords:** Psychosomatic therapy, Study protocol, Primary care, Randomised controlled trial, Medically unexplained symptoms, Cost-effectiveness

## Abstract

**Background:**

Medically unexplained symptoms (MUS) are highly prevalent and pose a burden both on patients and on health care. In a pilot study psychosomatic therapy delivered by specialised therapists for patients with MUS showed promising results with regard to patient’s acceptability, feasibility and effects on symptoms. The aim of this study is to establish whether psychosomatic therapy by specialised psychosomatic exercise therapists is cost- effective in decreasing symptoms and improving functioning in patients who frequently consult their general practitioner (GP) with MUS.

**Methods:**

A randomised effectiveness trial with an economic evaluation in primary care with 158 patients aged 18 years and older who are frequently consulting their GP with MUS. Patients will be assigned to psychosomatic therapy in addition to usual care or usual care only. Psychosomatic therapy is a multi-component and tailored intervention, aiming to empower patients by applying psycho-education, relaxation techniques, mindfulness, cognitive approaches and/or graded activity. Patients assigned to the psychosomatic therapy receive 6 to 12 sessions of psychosomatic therapy, of 30–45 min each, delivered by a specialised exercise or physical therapist.

Primary outcome measure is patient-specific functioning and disability, measured with the Patient-Specific Functional Scale (PSFS). Secondary outcome measures are symptom severity, consultation frequency and referrals to secondary care, patient satisfaction, quality of life and costs. Assessments will be carried out at baseline, and after 4 and 12 months.

An economic evaluation alongside the trial will be conducted from a societal perspective, with quality-adjusted life years (QALYs) as outcome measure. Furthermore, a mixed-methods process evaluation will be conducted.

**Discussion:**

We expect that psychosomatic therapy in primary care for patients who frequently attend the GP for MUS will improve symptoms and daily functioning and disability, while reducing consultation frequency and referrals to secondary care. We expect that the psychosomatic therapy provides value for money for patients with MUS.

**Trial registration:**

Netherlands Trial Register, ID: NL7157 (NTR7356). Registered 13 July 2018.

## Introduction

Medically unexplained symptoms (MUS) have been defined as symptoms of which the origins remain unclear after adequate history taking, physical examination and careful consideration of the psychosocial context by a physician [1]. These symptoms are common in primary and secondary care and are often accompanied by psychological, psychiatric and social(−economic) problems. Verhaak et al. estimated that 2.5% of the patients attending primary care can be classified as having persisting MUS [2]. Patients with persistent MUS suffer from their symptoms, are functionally impaired, have a lower quality of life and are at risk of undergoing unnecessary and possibly harmful tests, referrals and treatments [3, 4]. Therefore, these symptoms pose a major burden on patients and society with large societal costs, health care costs and costs of lost productivity [5]. Patients are often dissatisfied with the medical care they receive. They report that they experience a lack of empathy and support, feel stigmatised and not taken seriously, and are worried because neither they nor their physicians understand where the symptoms come from [6, 7].

General practitioners (GPs) often experience patients with MUS as difficult to manage. While many GPs consider MUS to be an expression of psychological distress, patients do not always see the connection between their symptoms and distress. GPs also experience problems in providing plausible explanations for the origin of the symptoms to their patients [8].

The mismatch between perceptions of GPs and patients as described above explains why patients with MUS are often dissatisfied with the medical care that they receive. Limited consultation time, lack of skills of the GP and patients’ resistance towards psychosocial attributions contribute to these difficulties [9].

In primary care, 10% of the patients consulting their GP account for between 30 and 50% of the consultations [10]. Compared to ‘normal’ attenders, these frequent attenders (FAs) generate five times as many prescriptions and hospital contacts and the mean number of GP consultations of persistent FAs compared to non-frequent attenders are seven-fold higher (10.2 and 1.4 visits per year, respectively) [11]. While a proportion of the FAs has one or more diseases that require frequent monitoring, a substantial number of FAs seek medical care for somatic symptoms not explained by physical disease (i.e. MUS) [12].

In the light of the high functional impairment that many of these patients experience, the risks of unnecessary diagnostic procedures and treatments, the problems that GPs face in the management of these patients and the high societal costs one might expect that evidence-based treatment strategies in primary care already exist. However, evidence on effectiveness of various pharmacological and psychological interventions in reducing symptoms and limitations is limited [13]. Several treatments for patients with MUS have been described. Specific interventions for patients with MUS applied in various settings are of limited value for primary care. A Cochrane review assessing the effects of non-pharmacological interventions for MUS concluded that when all psychological therapies included in the review are combined they seem to be superior to usual care or waiting list controls in terms of reduction of symptom severity [14]. However, effect sizes were small and only cognitive behavioural treatment (CBT) had been adequately studied as single treatment. Therefore, the review only allows tentative conclusions for daily practice. Moreover, most patients do not accept CBT as treatment for their MUS. The authors of the review state that the number of studies investigating treatment modalities other than CBT needs to be increased and that this is especially relevant for physical therapies [14].

Psychosomatic therapy is such a physical (multi-component) treatment, administered by physical and exercise therapists with special interest in MUS. It is a stepped-care and tailored approach in which (psycho)-education, relaxation therapy, mindfulness, cognitive behavioural therapeutic interventions and activating exercise therapy are key elements [15, 16].

The therapist explores and treats somatic symptoms by integrating the physical, cognitive, emotional, behavioural and social dimensions of health problems. The therapist explores underlying beliefs and psychosocial factors, which may influence the perceived somatic complaints, with the aim to give patients insight into the interaction of these factors with the somatic complaints and thus to empower patients to regain control over their own health.

Aspects of approaches incorporated in psychosomatic therapy have been shown to be effective in several studies [17–19]. A combination of cognitive behavioural intervention or psycho-education on one hand and exercise therapy on the other was found to reduce pain and fatigue and to increase physical functioning and quality of life in patients with MUS [20]. Our recent pilot randomised trial on the feasibility and treatment effects of psychosomatic therapy showed promising results with regard to patients’ acceptability, feasibility in daily GP practice and effects on symptoms [21]. A Dutch observational before-and-after cohort study by van Ravensberg and van Berkel in 119 patients with MUS demonstrated that patients improve significantly after psychosomatic therapy on self-rated symptom severity, symptoms of distress, quality of life, level of functioning, sick leave and use of medication [22].

Given the abovementioned challenges and lack of evidence, expanding the evidence base for cost-effective approaches in primary care is urgently needed. In order to guarantee optimal health care for patients who frequently attend with MUS in primary care, we aim to study the cost-effectiveness of psychosomatic therapy.

We will evaluate the effects and costs of psychosomatic therapy in primary care for patients who frequently attend the GP for MUS in improving symptoms and daily functioning and disability, while reducing consultation frequency and referrals to secondary care.

In addition to the quantitative (cost-)effectiveness study, we aim to perform a mixed-methods process evaluation to: (1) identify which treatment elements are actually applied; (2) identify the most effective elements of psychosomatic therapy; (3) understand which specific patients can benefit from this approach and (4) explore patients’ experiences with psychosomatic therapy.

## Methods: design, participants, intervention and outcomes

### Study design

The development of this protocol is in accordance with the Standard Protocol Items, Recommendations for Interventional Trials guideline (SPIRIT 2013) [23]. For the SPIRIT Figure see Fig. 1 and for the SPIRIT Checklist see Additional file 1.

**Fig. 1 Fig1:**
[figure not shown]
Schedule of enrolment, interventions and assessments. *PST* psychosomatic therapy; *CAU* care as usual; *PHQ-15* Patient Health Questionnaire 15-item somatic symptom scale; *PSFS* Patient Specific Functioning Scale; *iMCQ* iMTA Medical Consumption Questionnaire; *iPCQ* iMTA Productivity Cost Questionnaire; *NRS* numeric rating scale; *SF-36* Short Form Health Survey-36 items; *4DSQ* Four Dimensional Symptom Questionnaire; *GPE* Global Perceived Effect; *IAS* Illness Attitude Scale; *IPQ-B* Brief Illness Perception Questionnaire; *SRS-DV* Session Rating Scale Dutch version; *WAI-SF* Working Alliance Inventory short form; *1* only intervention group, directly after first session; *2* only intervention group directly after last session

We will perform a pragmatic randomised effectiveness trial with economic evaluation in primary care with patients aged 18–80 years who frequently, i.e. twice or more in the past months, consult their GP for MUS. Details regarding recruitment are presented below (see ‘Recruitment of study participants’ section). Patients will be individually randomised into intervention (psychosomatic therapy in addition to usual care) or control condition (usual care alone). The intervention (psychosomatic therapy) consists of 6 to 12 sessions, depending on number and severity of the patient’s symptoms, each of 30–45 min. Therapy will be delivered by a qualified psychosomatic therapist. The primary outcome measure will be functioning and disability measured with the Patient-Specific Functional Scale (PSFS) [24]. All patients will be followed for 1 year and will be asked to complete questionnaires at baseline and at 4 and 12 months’ follow-up. Participants in the intervention group will be referred to one of the 26 participating qualified psychosomatic therapists, physiotherapists or exercise therapists with a special interest in MUS, who receive a training for this study.

Parallel to the trial, patients who do not consent to randomisation (e.g. due to a strong preference for one of the treatment options) will be asked to complete the same questionnaires, to monitor outcome in this group of patients. The aim of this parallel group is to learn about the differences in patient characteristics at baseline and the course of MUS between the patients in the randomised trial and patients who do not want to participate in the randomised trial in order to better assess the generalisibility of the trial results. In this group of patients no interventions will be carried out on behalf of the investigators, but similar baseline and follow-up measurements will be conducted as in the randomised trial. Figure 2 presents the flow chart of the study with an overview of the inclusion procedure.

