**Fig. 3 Fig3:**
[figure not shown]
Graphical representation of the assumed working mechanism of psychosomatic therapy. **RET* Rational Emotive Therapy*, NLP* Neuro Linguistic Programme*, ACT* Acceptance and Commitment Therapy

For this study a standardised treatment protocol is developed, but the therapists are allowed to change the intensity, frequency and order of the elements in order to deliver personalised care. The psychosomatic therapists will receive an intensive training, an accredited e-learning and two meetings of 4 h each, focussed on MUS, information about the study and the standardised treatment protocol. The patient will not be restricted in seeking other care.

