### Sample size and power calculation

The main aim of our study is to establish whether, compared to usual care, psychosomatic therapy improves daily functioning, disability and symptoms, while reducing costs.

Calculations of sample size are based on a minimally relevant difference (mrd) between the two arms of 1 point on the PSFS (range 0–10) [32], with a standard deviation (sd) of 2 points, with an alpha of 0.05 and a power of 0.80. With an estimated dropout rate of 20% after 1 year at least 79 patients per treatment arm need to be included. With this sample size, we can also detect differences in perceived symptom severity (measured on a visual analogue scale (VAS); mrd = 1.3; sd = 2.6) and number of consultations (mrd = 3; sd = 4).

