#### Effect evaluation

##### Effectiveness of the intervention

Differences in the change scores between the intervention group and the control group on the primary and secondary outcomes will be analysed with multilevel (mixed-model) linear regression analyses taking all three measurements into account (baseline, and at 4 and 12 months). We will use a model with a random intercept and all other variables fixed.

A sensitivity analysis will be performed by replacing missing values by multiple imputation. *P* values < 0.05 are considered statistically significant.

Differences in the change scores between the cohort study group and both the intervention group and the control group on the primary, secondary and other study parameters will be analysed with multilevel (mixed-model) linear regression analyses, taking all three measurements into account. We will perform subgroup analyses for severity, duration and number of the symptoms and comorbidity to explore which patients are most likely to benefit from the intervention.

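### Intervention patients are nested in 26 therapists, but the model has no therapist term and the sample size assumes independence; with any within-therapist correlation the standard error is somewhat too small

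*Protocol article*

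**What the plan says.** Patients are randomised individually, and only those in the intervention arm meet a study therapist: "Participants in the intervention group will be referred to one of the 26 participating qualified psychosomatic therapists" (protocol article, Study design). Under Psychosomatic therapy, a standardised treatment protocol is announced, but "the therapists are allowed to change the intensity, frequency and order of the elements in order to deliver personalised care".

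The section Sample size and power calculation uses a "minimally relevant difference (mrd) between the two arms of 1 point on the PSFS", "with a standard deviation (sd) of 2 points, with an alpha of 0.05 and a power of 0.80". It then allows for 20% dropout and arrives at 79 per arm. It gives no intraclass correlation and no design effect.

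Under Effectiveness of the intervention, change scores are compared by mixed-model linear regression on baseline, 4-month and 12-month measurements: "We will use a model with a random intercept and all other variables fixed". The level of the intercept is not named, and therapist does not appear in the effect analysis.

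**The concern.** Treated patients share therapists and controls do not. Whatever one therapist does better or worse than another is common to that therapist's patients and adds variance to the intervention-arm mean. A model with one random term cannot carry both the repeated measures within a patient and the patients within a therapist. If the intercept is the patient, as the three measurements suggest, therapist variation is left out. If it were the therapist, the correlation of repeated measures would be left out instead.

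With a patient intercept only, any positive therapist ICC makes the standard error of the treatment effect too small. The confidence interval is then too narrow, the p-value leans towards declaring benefit, and the stated power is reached only if there is no clustering. The same model serves the primary and the secondary outcomes. Because the protocol fixes the random-effects structure, this concerns a stated rule and not a detail left for an analysis plan.

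**Working it through.** **Inputs from the protocol article.** Difference 1 point, SD 2, alpha 0.05, power 0.80, 20% dropout, 79 per arm (Sample size and power calculation); 26 therapists, intervention arm only (Study design). Sidedness is not stated; two-sided is assumed because it reproduces the stated number.

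**Assumptions (not in the protocol).** Therapist ICC of 0.02, 0.05 or 0.10; coefficient of variation (CV) of therapist caseload of 0 or 0.7; total SD of 2 in both arms; normal approximation.

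**1. The plan's own figure.** n = 2 × (1.960 + 0.842)² × 2² / 1² = 62.8, so 63 per arm. 63 / 0.80 = 78.75, so 79. The stated figure reproduces exactly under independence. With 63 per arm, SE = 2 × √(2/63) = 0.3563, and power = Φ(1/0.3563 − 1.960) = 0.801.

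**2. Adding therapist clustering in one arm.** Power is computed on analysed patients, so the caseload must be too: m = 63/26 = 2.42.

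- Design effect in the intervention arm: DE = 1 + (m(1 + CV²) − 1) × ICC. In the control arm it is 1.
- Variance inflation of the difference: F = (1 + DE)/2.
- SE = 0.3563 × √F.
- Power = Φ(1/SE − 1.960).
- True alpha of a test that ignores therapist = 2 × (1 − Φ(1.960/√F)).

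Example, ICC 0.05 and even caseloads: DE = 1 + 1.42 × 0.05 = 1.071; F = 1.036; SE = 0.3626; power = Φ(2.758 − 1.960) = 0.787; alpha = 2 × (1 − Φ(1.926)) = 0.054.

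| ICC | CV | DE | F | SE | Power | True alpha |
|---|---|---|---|---|---|---|
| 0.02 | 0 | 1.028 | 1.014 | 0.359 | 0.796 | 0.052 |
| 0.05 | 0 | 1.071 | 1.036 | 0.363 | 0.787 | 0.054 |
| 0.10 | 0 | 1.142 | 1.071 | 0.369 | 0.774 | 0.058 |
| 0.02 | 0.7 | 1.052 | 1.026 | 0.361 | 0.791 | 0.053 |
| 0.05 | 0.7 | 1.130 | 1.065 | 0.368 | 0.776 | 0.058 |
| 0.10 | 0.7 | 1.261 | 1.130 | 0.379 | 0.752 | 0.065 |

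**3. Could the baseline measurement make good the loss?** If SD 2 is the unadjusted follow-up SD, baseline adjustment multiplies the variance by (1 − ρ²), where ρ is the correlation of baseline with follow-up. The loss is offset when (1 − ρ²) × F = 1, that is, ρ = √(1 − 1/F). With even caseloads this is ρ = 0.19 at ICC 0.05 and ρ = 0.26 at ICC 0.10. The protocol gives no ρ and does not say whether SD 2 refers to follow-up or to change scores, so the offset is possible but not shown.

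**The case against.** The tempting reading is that the trial does not deliver its 80% power. The documents do not support that as a flat statement. It depends on an ICC and a caseload spread that the protocol does not give. At ICC 0.05 with even caseloads the loss is 1.4 points (0.801 − 0.787), and a modest baseline correlation could cancel it. Pairing 79/26 = 3.04 randomised patients per therapist with 63 analysed per arm would also overstate the loss, because it mixes two populations.

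Other points for the plan:

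- The Discussion says that common training is meant to reduce differences between therapists. The flexibility allowed is for tailoring to the patient, which need not create variation between therapists. Both argue against a high ICC; neither shows that it is zero.
- The process evaluation intends to interview all 26 therapists after one of their first three patients. That fits a spread caseload better than a few therapists treating most patients, although nothing in the protocol balances caseloads.
- With 2.42 analysed patients per therapist the therapist variance is poorly estimated. By an ANOVA-type estimate it would come out at or below zero in roughly 38% of trials at ICC 0.05. The added term would then often change nothing, and a sensitivity analysis could also be defended.
- The level of the intercept is inferred, and a separate analysis plan may exist.

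These points limit the size and certainty of the problem. They do not remove it: a gain in power from baseline does not correct the type I error, and a plan that added a therapist effect would depart from the single random term fixed here.

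**Conclusion.** The structural point holds. The design is partially nested, the 79 per arm contains no allowance for it, and the stated model has no place for therapist. The consequence is conditional on a positive ICC and is modest.

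Over assumed ICCs of 0.02 to 0.10, power is about 0.80 to 0.77 with even caseloads and 0.79 to 0.75 at CV 0.7. True alpha is 0.052 to 0.058 and 0.053 to 0.065 respectively. It would become material only with a high ICC or with patients concentrated in few therapists. All of this is before any gain from the baseline measurement. It merits a correction to the model and to the power statement, not a redesign.

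**What to change.** 1. State that the random intercept is at patient level.
2. Add a therapist random effect that acts in the intervention arm only, with controls treated as singletons, and use Satterthwaite or Kenward-Roger degrees of freedom. Because baseline is one of the three modelled measurements and precedes therapy, let the therapist effect act on the follow-up measurements: an intercept shared with baseline would cancel from the change.
3. Pre-state a fallback to the patient-only model if the therapist variance is estimated at zero.
4. In the sample-size section, say that 0.80 assumes no therapist clustering and give the figure under a stated ICC: about 0.78 to 0.79 at ICC 0.05, before any gain from baseline adjustment, which depends on a correlation that the protocol does not give.

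Do not enrol more patients for this reason.

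The cost is a few sentences. Therapists already register their treatment data per patient (Process evaluation, Quantitative data), so the link from patient to therapist should be available. The drawbacks are slightly wider confidence intervals and a weakly estimated variance component.

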**Fig. 2 Fig2:**
[figure not shown]
Overview of inclusion procedure. *GP* general practitioner; *PHQ-15* Patient Health Questionnaire

Since we consider the psychosomatic therapy to be a complex intervention, we will conduct a process evaluation with quantitative and qualitative methods (mixed-methods) [25]. For the framework of the process evaluation we will use the approach described by Saunders et al., describing five components of process evaluation: fidelity, dose, reach, recruitment and context [26]. The aim of the process evaluation is to explore the mechanism of the intervention, the patients’ experiences with the psychosomatic therapy and understand which patients will benefit most from this therapy.

### Inclusion and exclusion criteria

Patients will be eligible for the study if they are aged 18 years or older, have visited their GP frequently in the last 2 years and have reported one or more ‘Robbins List’ symptoms in the past months [27]. Patients will be excluded from participation in the study if they are older than 80 years, have a Patient Health Questionnaire 15-item somatic symptom scale (PHQ-15) score of < 5 [28, 29], receive palliative care, have a severe psychiatric disorder (i.e. psychosis-related disorders, dementia and bipolar disorder), have a somatic or psychiatric disorder explaining their symptoms, are according to their GP not eligible for psychosomatic therapy or have insufficient understanding of the Dutch language.

Patients can withdraw from the study at any time for any reason without any consequences.

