### Recruitment of study participants

The patients will be recruited from general practices participating in the Academic Network of General Practices of the VU Medical Center (ANH-VUmc), the Academic General Practices Network Academic Medical Center (AHN-AMC) and the Radboud University Medical Center Academic General Practices Network (Radboudumc-AHN). If the number of inclusions from these networks of general practices proves to be insufficient we will approach other general practices in the Netherlands (in and around Amsterdam and Nijmegen).

Eligible patients will be identified by a search strategy that selects from the electronic medical records those patients (aged 18 to 80 years) who visited their GP frequently over the past 2 years with MUS, based on a list of 23 unexplained physical complaints composed by Robbins et al. [27]. Patients who visited their GP twice or more in the past months with one or more Robbins List symptoms are eligible. Table 1 presents the Robbins List with 23 physical complaints. The GP will screen the selected list of this frequently attending group patients for potential exclusion criteria and/or other pertinent reasons for not inviting them, such as a terminal disease or insufficient understanding of the Dutch language. In addition to the search strategy, participating GPs will be asked to enrol eligible MUS patients who are not present on the selected list. The identified and screened potential participants not meeting exclusion criteria will be approached by their GP who sends them a package containing a letter with brief information about the study, the PHQ-15, a brief consent form to receive more information about the study and an addressed return envelope. The PHQ-15 is a frequently used and validated questionnaire about physical symptoms [29]. It consists of 15 items, each of which can be scored from 0 (‘not bothered at all’) to 2 (‘bothered a lot’), which results in a total score ranging from 0 to 30. Higher scores indicate higher somatic symptom severity. Scores of 5, 10 and 15 represent cut-off points for low, medium and high somatic symptom severity, respectively [28].

**Table 1 Tab1:** Symptoms from the Robbins List [27]

1. Back pain	
2. Joint pain	
3. Extremity pain	
4. Headaches	
5. Weakness	
6. Fatigue	
7. Sleep disturbance	
8. Difficulty concentrating	
9. Loss of appetite	
10. Weight change	
11. Restlessness	
12. Thoughts slower	
13. Chest pain	
14. Shortness of breath	
15. Palpitations	
16. Dizziness	

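### The frequent-attendance criterion is worded in three ways that do not agree, so who is eligible depends on which section is applied

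*Protocol article*

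**What the plan says.** Three sections of the protocol article define the criterion.

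- **Study design** (text after Fig. 1): the trial takes patients "who frequently, i.e. twice or more in the past months, consult their GP for MUS". The number of months is not given.
- **Inclusion and exclusion criteria**: patients must "have visited their GP frequently in the last 2 years and have reported one or more" Robbins List symptoms in recent months. No visit count is attached to the 2 years, and the visits need not be for MUS.
- **Recruitment of study participants**: the record search selects those "who visited their GP frequently over the past 2 years with MUS, based on a list of 23 unexplained physical complaints". The next sentence reads "Patients who visited their GP twice or more in the past months with one or more Robbins List symptoms are eligible".

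The recruitment section also opens a second route: "participating GPs will be asked to enrol eligible MUS patients who are not present on the selected list".

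For scale, the Introduction gives mean GP consultations for persistent frequent attenders and for non-frequent attenders as "10.2 and 1.4 visits per year, respectively". The sample size section says the trial can also detect a difference of 3 in the number of consultations, with a standard deviation of 4. The secondary outcomes section promises change from baseline for every secondary outcome, but the GP is asked only for the consultation total in the year following therapy.

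**The concern.** Frequent attendance is in the trial's title and defines its target population, and fewer consultations is one of its stated aims. If the sections give different rules, two practices, or the search route and the GP route, can each follow the article and still enrol different patients. A reader of the results could then not say to whom they apply.

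The secondary consultation outcome is exposed as well. A patient who attends about as often as a non-frequent attender has little room to consult less, so admitting such patients would dilute any effect on that outcome.

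**Working it through.** **1. The wordings side by side**

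| Place | Visit count | Window | Visits for what | Separate symptom condition |
|---|---|---|---|---|
| Study design | two or more | months, number not given | MUS | none |
| Inclusion criteria | none | 2 years | any reason | at least one Robbins symptom, in months, number not given |
| Recruitment, search sentence | none | 2 years | MUS, by Robbins List | none |
| Recruitment, eligibility sentence | two or more | months, number not given | Robbins symptom | none |

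**2. Two test patients**

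*Patient A* has many visits over 2 years to monitor a disease that does not explain the symptom, and one recent visit with a Robbins symptom.
- Inclusion criteria: met.
- Study design: not met (one MUS consultation, two needed).
- Recruitment: not met (the frequent visits were not for MUS, and there is only one recent Robbins visit).

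*Patient B* has two recent visits for unexplained fatigue and no earlier attendance in the 2 years.
- Study design: met.
- Inclusion criteria: met only if two visits in 2 years counts as frequent.
- Recruitment: met if the eligibility sentence stands alone; probably not met if the 2-year search must also be passed.

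Patient A shows a contradiction. Patient B shows an ambiguity.

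**3. How many ordinary attenders could reach two visits**

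Inputs: 1.4 and 10.2 visits per year (Introduction). The window of m months is not stated, so a range is assumed. With Poisson visits, μ = rate × m/12 and P(at least 2) = 1 − e^(−μ)(1 + μ).

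- m = 3: μ = 1.4 × 3/12 = 0.35; P = 1 − 0.7047 × 1.35 = 0.049.
- m = 6: μ = 1.4 × 6/12 = 0.70; P = 1 − 0.4966 × 1.70 = 0.156.

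| Window (months) | 1.4 per year, Poisson | 1.4 per year, negative binomial, shape 1 | 1.4 per year, half of visits for Robbins symptoms, Poisson | 10.2 per year, Poisson |
|---|---|---|---|---|
| 2 | 2.3% | 3.6% | 0.6% | 50.7% |
| 3 | 4.9% | 6.7% | 1.4% | 72.3% |
| 6 | 15.6% | 17.0% | 4.9% | 96.3% |
| 12 | 40.8% | 34.0% | 15.6% | about 100% |

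The negative binomial column checks overdispersion. The halving is an assumption, since the article gives no such share. The all-visit columns overstate entry, because the visits must concern Robbins symptoms and the patient must also pass GP screening and score at least 5 on the PHQ-15. A 12-month window already stretches 'the past months', so longer ones are not considered.

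**4. Does this touch the primary sample size?**

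With a PSFS difference of 1, SD 2, two-sided alpha 0.05 (two-sidedness assumed) and power 0.80: n = 2 × (1.96 + 0.84)² × 2²/1² = 62.7, so 63 per arm. Then 63/0.80 = 78.75, so 79, as stated. The attendance rule enters nowhere.

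**5. The consultation outcome**

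A patient at 1.4 visits per year cannot fall by 3 visits per year. The difference of 3 is a between-arm mean, so this shows limited room in such patients; it does not show that the difference is unattainable in the trial.

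**The case against.** The best defence is that the recruitment section is the operational text. Study design is a summary that refers the reader to it. Its sentences can be read as cumulative: the search finds 2-year frequent attenders with MUS, two recent Robbins visits are then required, and the GP screens the resulting list. This is the natural reading, and it stands. A reader might infer that someone with two visits and no earlier attendance is plainly eligible under that section; the text does not support that. The defence does not rescue the formal criteria, which still admit Patient A.

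Other points in the plan's favour also stand.

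- Only one visit count, two, appears anywhere. The mismatch is between that count and an uncounted 'frequently', not between rival counts.
- A reader might infer that the two-visit rule fails to select frequent attenders by the article's own figures. That cannot be said without the window. The two rates are means for visits of any kind, whereas the rule sets a minimum on Robbins-symptom visits only. With a short window, few ordinary attenders would meet it.
- GPs are asked to add eligible patients, so the criteria do bind the second route. The difficulty is that 'eligible' leads back to wordings that disagree.
- The inclusion flow chart (Fig. 2) and the full protocol are not at hand and may give the count and the number of months. They could fill a gap, but they cannot make three published wordings agree.

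**Conclusion.** The point holds as an inconsistency in the criterion that defines the population. The formal criteria conflict with both Study design and the recruitment section, and Patient A shows it without any assumption.

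Entry of ordinary attenders is a possibility, and it is conditional on the two-visit sentence being used alone. Its size depends on the unstated window: about 5% of people at 1.4 visits per year reach two visits in 3 months and about 16% in 6 under Poisson (about 7% and 17% with the overdispersion tested), before the Robbins, GP and PHQ-15 filters. Those filters select on symptoms and suitability, not on attendance, so they shrink the number but do not restore the criterion.

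The consequences are for reproducible screening, for the population to which the result applies, and for the secondary consultation outcome. A reader might infer that the primary comparison is compromised. It is not: randomisation is individual, and the PSFS sample size and alpha do not depend on the rule. The point should be corrected, but it does not undermine the trial.

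**What to change.** 1. Put one rule in Study design, Inclusion and exclusion criteria, and Recruitment of study participants, with a visit count and a window in numbered months. Say whether the 2-year search and the two-visit condition must both be met, and whether the visits must be for Robbins symptoms. As recruitment began in January 2019, also document the rule applied so far.
2. Apply the same rule, with the same record check, to patients whom GPs add outside the search.
3. From the records already searched, store each patient's consultation count before baseline and the recruitment route (search or GP).
4. Adjust the consultation outcome for that prior count. This also supplies the baseline that the secondary outcomes section relies on but does not describe for GP consultations.

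The cost is amendment wording and a small amount of extra record extraction. No new attendance threshold is proposed, because that would change the population after recruitment has started.
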